### Participants

#### Inclusion criteria

Patients fulfilling all the following inclusion criteria will be selected as study volunteers:Patients meeting the diagnostic criteria of AECOPD: post-bronchodilator forced expiratory volume in 1 s (FEV_1_)/forced vital capacity (FVC) < 0.70; exacerbation comprising respiratory symptomatic worsening and beyond normal day-to-day variations that lead to a change in medication; (GOLD 2016 [17]).Existing indications for potential admission: the symptoms significantly worsening; severe underlying COPD (respiratory muscle fatigue, paradoxical respiration, aggravated or new centralized cyanosis, peripheral edema, unstable hemodynamic and mental state deterioration); new physical signs; failure of initial medical management of acute exacerbation; presence of serious complications; frequent exacerbation; older age; and insufficient domestic support (GOLD 2016).Age between 40 and 85 years, male or female.Weight between 40 and 100 kg.Signed informed consent.

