#### Secondary outcome measures

The secondary outcome measures will be:Changes in immune indicators (detected by flow cytometry).Changes in inflammation indicators (detected by enzyme-linked immunosorbent assay).Respiratory support: the duration of oxygen therapy, high-flow humidification oxygen therapy, noninvasive mechanical ventilation, and invasive mechanical ventilation.Mortality rate after 28 days.Blood gas analysis (including blood lactate).Improvement in acute physiology and chronic health evaluation II (APACHE II) scores; the evaluation of improvement is based on differences in the APACHE II scores before and after the intervention.Improvement in clinical symptoms based on improvement in dyspnea, cough, sputum, and the use of accessory respiratory muscles (using the scoring system shown in Table 2). According to the differences in the scores before and after the intervention, the evaluation criteria are as follows:Significantly effective: the score decreased ≥ 3;Effective: the score decreased from 1 to 3;Ineffective: no change in the score;Exacerbation: the score increased ≥ 1;Name, dosage, and duration of antibiotic use.Name, dosage, and duration of corticosteroid use.Changes in laboratory inspection indicators.Incidence of complications.Length and cost of intensive care unit (ICU) stay.Length and cost of hospitalization.

**Table 2 Tab2:** The clinical symptoms scoring system of AECOPD

Score	Dyspnea	Cough	Sputum production	Use of accessory respiratory muscles
0	–	No cough	No sputum	No neck muscle tension and periodic contraction
1	Shortness of breath when flat on the ground or walking up one floor level	Intermittent cough, but no symptoms at night	Sputum volume ≤ 30 mL the whole day and night	Neck muscle tension, but no obvious muscle activity
2	Shortness of breath when walking with peers	Sometimes cough, which probably affects sleep	Sputum volume ≥ 30 mL and ≤ 50 mL	Visible slight contraction of the neck muscles
3	Need to stop so as to breathe when walking at their own speed	Frequent cough affecting sleep	Sputum volume ≥ 50 mL and ≤ 100 mL	Moderate contraction of the neck muscles, not with clavicular fossa and intercostal retraction
4	Shortness of breath when dressing or undressing	–	Sputum volume ≥ 100 mL	Strong contraction of the neck muscles, with abdominal contradictory movement

The evaluation criteria for the improvement in clinical symptoms is according to the total scores of the 4 items

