### Statistical analysis

An independent professional statistician and researcher will develop a complete statistical analysis plan for the trial, prior to the final analysis. The statistical analysis will be performed by the statistician in a blinded manner using the Statistical Analysis System (SAS) software version 9.2. The main analysis will be based on the full analysis set (FAS). According to the intention-to-treat principle, the FAS refers to a set of data on any participants who randomly receive at least one treatment. The per-protocol set (PPS), a subset of the FAS, includes data on only those participants who completed the trial without any violations of or deviations from the protocol. The FAS and PPS will be used for the assessment of efficacy. For the safety assessment, the safety set (SS) will be used, which includes patients who have received at least one safety evaluation after treatment.

All data, including the number of subjects included, drop-outs, elimination conditions, demographics, baseline characteristics, and efficacy and safety assessment, will be analyzed using different approaches. Descriptive and univariate statistics will be used to characterize the study participants and compare the baseline characteristics between the two groups. The primary outcome is the rate of endotracheal intubation, which will be determined by the Cochran-Mantel-Haenszel (CMH) test in the FAS population. We prefer to use the CMH chi-square test because it can deal with confounders of multi-center effects. Two-sided tests will be performed for all the other statistical analyses. The CMH chi-squared test or Fisher’s exact test will be used for comparing the categorical outcomes. The continuous outcomes will be analyzed by Student’s *t* test, while the AEs will be presented using descriptive statistics and compared using a chi-square test. A *P* value <0.05 will be considered to indicate statistical significance. Missing data will be explored and adjusted using the imputation method.

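### The symptom score is cut into four classes that overlap at a 3-point fall and leave no room for ordinary variation, which costs power against analysing the total as a number (minor)

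*Protocol article*

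**What the plan says.** All references are to the protocol article.

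- **Score.** Table 2 grades dyspnea, cough, sputum and accessory-muscle use. The table note says: "The evaluation criteria for the improvement in clinical symptoms is according to the total scores of the 4 items". As printed, the maximum is 4 + 3 + 4 + 4 = 15.
- **Classes (Secondary outcome measures).** "According to the differences in the scores before and after the intervention, the evaluation criteria are as follows". The four classes are "Significantly effective: the score decreased ≥ 3"; "Effective: the score decreased from 1 to 3;Ineffective: no change in the score"; and "Exacerbation: the score increased ≥ 1".
- **Test (Statistical analysis).** The CMH chi-squared test or Fisher's exact test "will be used for comparing the categorical outcomes"; continuous outcomes go to Student's *t* test. The version of the CMH test is not named.
- **Entry (Inclusion criteria).** The diagnosis requires "exacerbation comprising respiratory symptomatic worsening and beyond normal day-to-day variations that lead to a change in medication".
- **Timing (Follow up).** Data are recorded on each of the five treatment days, then on days 6 and 28. The schedule figure is not shown.

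The article gives no SD, repeatability, expected class distribution or power for the symptom score.

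**The concern.** Three features of the classification work against it.

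1. **The classes are not mutually exclusive.** A fall of exactly 3 is both *Effective* (1 to 3) and *Significantly effective* (3 or more).
2. **There is no band for ordinary variation.** One item moving by one grade takes a stable patient out of *Ineffective*. Table 2 makes such steps easy: 30 mL of sputum fits grades 1 and 2, 50 mL fits 2 and 3, and 100 mL fits 3 and 4, while two cough grades turn partly on whether the cough is intermittent or occurs sometimes. The diagnosis at entry recognises day-to-day variation; the definition of response does not.
3. **Size of change is discarded.** Falls of 3 and of 10 count the same. Patients enter during an acute exacerbation and both arms receive full routine treatment, so many in both arms may reach the top classes, where the classes can no longer separate the arms.

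At stake are the meaning of the reported class percentages, which cannot be read as treatment response, and the precision of the symptom comparison. By contrast, the same section evaluates APACHE II improvement from the score difference and does not class it.

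**Working it through.** **The plan's own figure.** The article has no calculation for the symptom score. Its only one is the primary sample size, which supplies the 150 per arm used below. With rates 0.152 and 0.047 (mean 0.0995), two-sided α = 0.05 and power 80%:

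n = [1.96·√(2 × 0.0995 × 0.9005) + 0.8416·√(0.152 × 0.848 + 0.047 × 0.953)]² / 0.105² = (0.8297 + 0.3508)² / 0.011025 ≈ 126.4, so 127. Then 127 / 0.85 = 149.4, so 150. Both stated figures reproduce.

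**Step 1: patients with no true change.** The reading error is an assumption, so a range is shown.

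(a) Let the observed difference be normal with mean 0 and SD *s*, rounded to whole points. Then P(fall ≥ 1) = Φ(−0.5/*s*).

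| *s* (assumed) | 0.3 | 0.5 | 0.75 | 1.0 | 1.5 | 2.0 |
|---|---|---|---|---|---|---|
| *Effective* or better | 5% | 16% | 25% | 31% | 37% | 40% |

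(b) Let each of the four items, at each of two readings, be off by one grade with probability *q*, up or down equally. Convolving the eight errors gives the exact probability.

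| *q* (assumed) | 2% | 5% | 10% | 15% | 20% |
|---|---|---|---|---|---|
| *Effective* or better | 7% | 16% | 25% | 30% | 33% |

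Both models are symmetric, so the same share falls in *Exacerbation*. The error does not depend on arm.

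**Step 2: the overlap at 3.** Let the change be rounded normal with SD 2.5 (assumed). The share with a fall of exactly 3 is the probability between 2.5 and 3.5:

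- mean fall 0: Φ(1.4) − Φ(1.0) = 0.919 − 0.841 = 8%
- mean fall 3: 2Φ(0.2) − 1 = 16%
- mean fall 5: Φ(1.0) − Φ(0.6) = 0.841 − 0.726 = 12%

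So about 8% to 16% of patients would have no unique class.

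**Step 3: power.** Assumed: 150 per arm, SD of change 2.5, benefit 0.8 points, two-sided α = 0.05. For the numeric change, rounding to whole points makes the SD √(2.5² + 1/12) = 2.517. Power is then about Φ(0.8 / (2.517·√(2/150)) − 1.96) = Φ(2.753 − 1.96) = Φ(0.793) = 79%. The class tests were simulated with 4,000 trials per setting, without centre strata, and with falls of 3 placed in the top class:

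| Mean fall, control arm | Numeric change (*t* test) | Four classes, ordinal score test | Four classes, unordered chi-square | Control arm *Effective* or better |
|---|---|---|---|---|
| 0 | 78% | 70% | 54% | 42% |
| 1 | 79% | 71% | 54% | 58% |
| 2 | 78% | 67% | 51% | 73% |
| 3 | 79% | 62% | 47% | 84% |
| 4 | 78% | 52% | 37% | 92% |
| 5 | 79% | 39% | 24% | 96% |

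The last column is Φ((mean fall − 0.5)/2.5). Separate simulations of the same settings agree within about 2 percentage points; one gives 26% in the last unordered cell. Every class test has less power than the numeric change in every row, and the gap widens as recovery becomes general.

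**The case against.** The strongest case against has five parts.

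- **Numeric analysis is not excluded.** The class is built from a score difference, so the number exists; the article gives a *t* test for continuous outcomes and promises a full analysis plan. This is true. But the outcome as defined is the set of classes, and categorical outcomes are assigned to categorical tests, so the text as it stands leads to the weaker analysis.
- **Randomisation and blinding deal with noise and recovery.** This stands. Both fall on the two arms alike, so no false difference arises. The cost is dilution and lost precision.
- **The entry wording defines an exacerbation and says nothing about the repeatability of the Table 2 score.** This also stands. The contrast illustrates the missing band; it does not measure it.
- **The noise and recovery arguments pull apart.** If nearly everyone recovers, few patients are unchanged. That is fair: the two problems bite in different settings and their sizes should not be added.
- **It is one of 13 secondary items with no power claim attached.** This stands and sets the severity.

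Some stronger readings are tempting. A reader might infer that noise makes some fixed share, say 30%, of unchanged patients responders; that figure holds only near *s* = 1 or *q* = 15%, and neither is in the documents. A reader might infer that most of the power is lost; the ordinal test keeps at least half of it in every row above, and losses beyond half need the unordered test, or a collapse to any fall of 1 or more, together with large common recovery. Nor does the article say that response rests on a single reading, or that the two top classes are pooled into a responder rate.

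**Conclusion.** The point holds as a minor one. Two parts rest on the text alone: the classes overlap at a fall of exactly 3, and they leave no band for ordinary variation. The size of the second is not known from the documents; roughly 5% to 40% of truly unchanged patients is a range under assumed reading errors. That classing loses power held in every setting examined, but the amount depends on the assumed SD, benefit and common recovery and on which CMH version is used. Against about 78% for the numeric change, it is about 70% down to 39% with an ordinal test and about 54% down to 25% with an unordered one. The consequence is a less sensitive symptom comparison and class percentages that are hard to interpret. It is not bias in favour of either arm, and the primary outcome is untouched.

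**What to change.** - In Secondary outcome measures and Statistical analysis, name the total symptom score after the intervention (day 6) as the analysed symptom outcome. Compare it between arms as a number, for instance by a linear model with the entry total and centre as covariates, and report the difference in points with its confidence interval.
- Keep the four classes as description only, and reconcile their boundaries so that a fall of exactly 3 has one class.

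A confirming reading on days 5 and 6, or a wider no-change band, is not recommended. No figure in the documents supports a band width. Under Precautions, the data of a patient who stops early are entered as day 6 from the first day of withdrawal, so a separate day-5 reading may not exist.

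**Cost.** Wording only, assuming the symptom score is among the items recorded at entry and on day 6 (the schedule figure is not shown). The downside is that the class percentages are no longer the tested result and are less directly comparable with earlier reports that use the same classes.

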### Follow up

Various parameters are followed up according to the data collection time points (Fig. 2).Screening period (1 day): 24 h before recruitment.Intervention period (5 days): follow up and recording of data every dayPeriod after intervention (within 28 days after treatment): follow up on days 6 and 28. If the patient is discharged, contact is established via telephone or a short messaging service.

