**Methods:**

This study will be a prospective, randomized, placebo-controlled, blinded, multi-center trial. A total of 300 eligible patients will be randomly assigned to the treatment or placebo control group in a 1:1 ratio using a central randomization system. The treatment group will receive routine medication plus XBJ injection, and the control group will receive routine medication plus 0.9% NaCl injection. The patients will receive the corresponding treatment for 5 days starting within 24 h of enrollment. The primary outcome, the of rate endotracheal intubation, will be evaluated on day 28 after treatment. The secondary outcomes will include changes in immune and inflammatory indicators, respiratory support, mortality rate after 28 days, blood gas analysis, improvement in Acute physiology and chronic health evaluation (APACHE) II scores and clinical symptoms, and the length and cost of intensive care unit stay and hospitalization. The safety of the interventions will be assessed throughout the trial.

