#### Precautions

The following precautions will be observed:The use of other injections simultaneously during the course of intravenous infusions is prohibited.Other injections should be separated into 50 mL 0.9% NaCl.Prohibited medicines include ulinastatin, and TCM injections, such as Tanreqing, Reduning, and Qingkailing with efficacy similar to that of XBJ.The routine treatment of AECOPD should be carried out simultaneously, and XBJ injection should not be used as a substitute.If medication is administered for < 5 consecutive days and the patients’ clinical symptoms improve significantly resulting in discharge or the condition deteriorates, necessitating other treatments, the administration of the research medication will be suspended. The data for the first day of withdrawal will be recorded to day 6, and the follow up will be continued until day 28.

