### Outcome measures

#### Primary outcome measures

The primary outcome of this study will be the endotracheal intubation rate. Endotracheal intubation has been commonly used in clinical practice and is associated with successful recovery of the breathing function [29]. However, the intubation process is also associated with significant risks of ventilator-acquired pneumonia, barotrauma, and failure to wean from spontaneous ventilation [30, 31]. It likely reflects the severity of AECOPD, the patient’s length of hospital stay, and mortality [32, 33]. Intubation indications were defined by a set of objective criteria [17], avoiding the inconsistencies associated with intubation on clinical grounds. The formula for evaluation is as follows:$$ \mathrm{Endotracheal}\ \mathrm{intubation}\ \mathrm{rate}=\left(\mathrm{the}\ \mathrm{number}\ \mathrm{of}\ \mathrm{endotracheal}\ \mathrm{intubation}\ \mathrm{cases}\right./\left.\mathrm{total}\ \mathrm{number}\ \mathrm{of}\ \mathrm{cases}\right)\times 100\% $$

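### Day-28 intubation and death may be followed up by text message after discharge, so missing outcomes may be informative, and the article both excludes and imputes patients with missing main data

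*Protocol article*

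**What the plan says.** The Primary outcome measures section states: "The primary outcome of this study will be the endotracheal intubation rate". The abstract says that it "will be evaluated on day 28 after treatment". The Secondary outcome measures section lists "Mortality rate after 28 days".

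Treatment lasts 5 days. After it, the Follow up section plans "follow up on days 6 and 28". For those no longer in hospital it adds: "If the patient is discharged, contact is established via telephone or a short messaging service". Under Precautions, when study medication stops early because of discharge or deterioration, "the follow up will be continued until day 28".

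Two places deal with a patient whose outcome is not obtained. The Withdrawal or dropout criteria list missing major data that affect evaluation of the main indicators among the reasons for not including a patient in the analysis. The Statistical analysis section bases the main analysis on the full analysis set (FAS), defined as randomised patients with at least one treatment, and says: "Missing data will be explored and adjusted using the imputation method".

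**The concern.** A patient discharged around the end of treatment has about three weeks of primary-endpoint time that rest on the day-28 contact. The wording lets that contact be a text message. Death, or being intubated on day 28, can itself prevent a reply, so silence may depend on the outcome being measured.

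What happens next depends on which section is followed. Under the withdrawal criteria a silent patient drops out of the analysis. Under the statistical section the patient stays and a value is imputed. If silence is more common among patients with events, exclusion under-counts events, and so does any imputation that relies on the patients who replied. At stake are power for the primary comparison and the accuracy of the intubation and mortality rates. Between-arm bias is a further possibility, but only if the two arms spend different amounts of time after discharge.

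**Working it through.** **The plan's own figure.** Inputs from the Sample size section: 15.2% versus 4.7%, two-sided α = 0.05, β = 0.2. With mean rate 0.0995 and pooled variance, no continuity correction:

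n = [1.960·√(2 × 0.0995 × 0.9005) + 0.842·√(0.152 × 0.848 + 0.047 × 0.953)]² / 0.105² = 126.4, so 127 per group.

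Allowing for 15% attrition, 127/0.85 = 149.4, so 150. Both stated figures reproduce, and neither is in dispute.

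**How many events there are to lose.** At the planned rates, 150 × 0.152 = 22.8 control events and 150 × 0.047 = 7.05 XBJ events. Losing 5% means about 1.1 and 0.4 events; losing 30% means about 6.8 and 2.1.

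**Equal loss in both arms.** The share f of events that occur after discharge and go unseen is an assumption, since the article gives nothing to estimate it. If those patients are missing, the observed rate is

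p′ = p(1 − f)/(1 − pf).

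For example, f = 0.10 in the control arm gives 0.1368/0.9848 = 13.89%. The table gives the exact two-sided power of the unstratified, uncorrected z test, keeping 150 per group as the denominator. The last column instead records lost events as no event, so that the rate is p(1 − f).

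| f | Control p′ | XBJ p′ | Power, patients missing | Power, recorded as no event |
|---|---|---|---|---|
| 0 | 15.20% | 4.70% | 88.0% | 88.0% |
| 5% | 14.55% | 4.48% | 86.6% | 86.1% |
| 10% | 13.89% | 4.25% | 84.9% | 83.8% |
| 20% | 12.54% | 3.80% | 81.0% | 78.5% |
| 30% | 11.15% | 3.34% | 76.1% | 72.2% |

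The usual normal approximation gives 86.3% rather than 88.0% with no loss, and 80.2% if attrition leaves 127 per group. The margin above 80% is thus largely the attrition allowance.

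**Unequal loss, shown only as a condition.** Suppose there is no true effect, 15.2% in both arms. With no loss, the chance of a significant result favouring XBJ is 2.5%. It is 2.9% if 2% of control and 4% of XBJ events are lost, 5.2% with 10% and 20%, and 10.6% with 10% and 30%. With equal losses of 10% in both arms it stays at 2.5%. Inflation therefore needs a difference between arms in what is lost.

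**The two missing-data rules.** A treated patient with no day-28 status belongs to the FAS by its definition and would be imputed. The same patient meets the withdrawal criterion for missing main data and would not be analysed. The article does not say that this criterion applies only to the per-protocol set.

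**The case against.** The strongest defence is that the Follow up sentence only names channels for making contact. It puts telephone first, and it does not say that a text reply alone settles day-28 status, that only the patient may answer, or that silence ends the enquiry. Next-of-kin numbers, call-back rules and record checks commonly sit in a full protocol or case report form, and the imputation method in the analysis plan, so their absence from an article is not a defect. Intubations during the index stay are seen directly. Patients discharged because they improved are probably at lower risk. Adverse events are to be recorded and sites monitored every two weeks. A 5% loss costs about 1.5 points of power, and in the missing-patient case even 20% leaves 81%.

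Most of this stands, and it limits the size of the point. It does not remove two things that the article itself states: text message is an accepted alternative to a call, and patients with missing main data are both left out and imputed. The withdrawal list may be meant for the per-protocol set, but it speaks of the analysis without that limit.

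Three stronger readings are tempting and are not supported:

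- That missing outcomes are in fact enriched for events. No non-response figure is given, and a relative may answer; the text supports only that they may be.
- That XBJ is expected to shorten the stay, so that the bias favours XBJ. Length of stay is only listed as a secondary outcome, with no direction. Blinding of investigators and evaluators also points to the same follow-up procedure in both arms.
- That an intubation elsewhere would be miscounted because its indication cannot be verified. The statement "Intubation indications were defined by a set of objective criteria" concerns indications; the outcome formula counts intubated cases whatever the indication.

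**Conclusion.** The point holds as a cheap improvement to a stated method, together with a contradiction to be resolved. The article permits text-message contact for an endpoint that can itself stop the patient replying, so missing day-28 outcomes may be informative, and its two rules for such patients disagree.

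The size cannot be known from the document. With assumed equal losses of 5% to 30% of events and those patients missing, power at 150 per group falls from 88% to between 87% and 76%; the true effect may lie at or below the small end. These figures rest on the planned rates, an unstratified test and 150 analysed per group. Bias between arms is conditional on different discharge timing, which the article does not state. The sample size needs no change.

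**What to change.** In the Follow up section, state that neither an unanswered contact nor a text message alone settles day-28 status. Take a next-of-kin telephone number at consent. On day 28, obtain vital status and intubation status by voice call with the patient or that relative. For non-responders and reported readmissions, check the hospital record.

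Reconcile the Withdrawal or dropout criteria with the Statistical analysis section: keep patients whose day-28 status stays unresolved in the FAS, and confine any exclusion for missing main data to the per-protocol set. Add one sensitivity analysis that counts unresolved patients as intubated, and for mortality as dead, in both arms.

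The cost is one more telephone number per patient, some calls and record checks by site staff around day 28, and one extra table.
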